#### Salivary α-Amylase

We will record α-amylase in U/mL. The concentration is derived from the same 7 salvia samples as used for the cortisol analysis and will be determined by a kinetic colorimetric test. The reagents for this will be obtained from DiaSys Diagnosic Systems.

#### Reproductive Hormones

Reproductive hormones (testosterone, estradiol, and progesterone) will be recorded in pg/mL. Four saliva samples will be collected using Salicaps (IBL International) at the measurement time points T0 (−11 min before the TSST-G), T1 (TSST-G onset), T3 (after the arithmetic task), and T6 during rest (+65 min after TSST-G onset). Hormone concentrations will be determined by biochemical analysis in the laboratory. The following kits from IBL will be used for analysis: Testosterone Luminescence Immunoassay, 17 beta-Estradiol Saliva Luminescence Immunoassay, and Progesterone Luminescence Immunoassay.

### Autonomic Nervous System

Heart rate and heart rate variability will be measured with a Polar H10 sensor (Polar Electro UK Ltd). The sensor is placed in a pulse belt that the participants will wear around their chest. With the help of a Polar station and an iPad, the participants’ data are transmitted wirelessly and in real time.

### Speech Performance

The participants will be videotaped while they complete the tasks (interview and arithmetic task) in front of the panel. The video sequences showing the recording of the interview will be coded for speech performance using a self-developed coding system. This system includes the following 3 quality criteria: the information content, the presentation style, and the perceived competence of the participants. The assessment of the information content is based on a checklist for the evaluation of a presentation according to Ascheron [70]. The content is scored on the following 5 items: “structure/organization,” “comprehensibility of content,” “flow,” “information content,” and “message.” These items will be rated on a scale that ranges from 1 (*very good*) to 6 (*unsatisfactory*). A modified questionnaire of Ascheron [70] will be used to evaluate the presentation style. The 2 items intonation and English quality were left out because intonation overlaps with another item (emphasis) and English quality is irrelevant because the study will be conducted in German. The presentation style is rated on the basis of the following 5 items: “speed,” “intelligibility,” “emphasis,” “body language,” and “eye contact,” whereby we added the latter item to complement the construct in more detail. The items will be scored using a 6-point scale (1, *very good* to 6, *unsatisfactory*). Since there is no suitable measurement tool for the assessment of perceived competence in the literature, we determined 5 items that should enable a differentiated evaluation of this construct. The following items will be scored on a 6-point scale: “technical language/vocabulary,” “use of filler words,” “use of everyday language,” “interest,” and “persuasiveness.” Construct validity of this competence scale will be checked.

### Data Management

The questionnaire data will be downloaded from Limesurvey and stored on the university server. The psychological questionnaire from T2, which will be collected by paper and pencil format, as well as heart rate and heart rate variability will be stored in an Excel table by the study experimenter directly after the study. The video file will also be saved directly after the experiment, on a laptop of the sport psychology laboratory and a back-up server. The saliva samples will be sent to the biochemical laboratory of the Institute for Medical Psychology in Heidelberg, Germany. To guarantee the accuracy of the analyses, 10% of the cortisol samples and 20% of the samples for reproductive hormones will be double assessed. The signed consent forms of the participants will be collected in the sport psychology laboratory in Constance. Only the experimenter will have access to the data, which will be stored for 10 years on a server of the University.

The participants will generate their own code that allows to merge the data of the web surveys with the data obtained in the laboratory.

Saliva samples will be stored in the biochemical laboratory at Heidelberg University Hospital for at least 2 years after completion of the study and will then be discarded.

### Statistical Analysis

Statistical analysis will be performed using IBM SPSS Statistics, Version 28 (IBM Corp) for Windows (statistical analysis and graphs). We will perform an analysis of variance with repeated measures to determine if the TSST procedure results in significant increases in psychological and biological variables for all participants. We will calculate multiple linear regressions to examine interaction effects. In these regressions, we will first include the control variables, then the condition as a dummy variable, and finally the individual predictors and their interaction terms. To account for repeated measurements of the collected hormones, the area under the curve with respect to increase will be calculated and used as a dependent variable [71]. As an additional effort to ensure that participants with a delayed significant increase in their hormones will not be excluded, an adjusted increase value will be calculated, regardless of the time of measurement. This value will be obtained by subtracting the baseline value from the peak value. Multiple regressions will be calculated again with these adjusted values. Nonbiological dependent variables, such as those obtained from the psychological test battery, will be added as means. Only data from individuals who have fully completed the TSST protocol will be included in the final analyses. Missing data will be added by multiple imputation.

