#### Hypothesis 1: Effect of Stress Induction Hypothesis

Participants in both groups (social support vs no social support) show an increase in stress responses comparable to that in previous studies. We expect a rise in the physiological parameter cortisol by at least 1.5 nmol/mL (Miller criterion) [57].

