### Sample Size and Recruitment

It is intended to recruit 154 participants (77 women). This sample size was calculated using a power analysis involving *G*Power 3.1* [58], with an additional 20% added to compensate for possible dropouts.

The recruitment will be done by flyer distribution in the University of Konstanz, as well as an entry in an online platform where experiments are offered by the departments of psychology and linguistics.

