#### Salivary Cortisol

The concentration of cortisol in saliva will be recorded in ng/mL. Seven saliva samples will be collected using Salicaps (IBL International) at measurement time points T0 (−11 min before the TSST-G), T1 (TSST-G onset), T2 (after the job interview), T3 (after the arithmetic task), and T4, T5, and T6 during the resting phase (+30 min, +45 min, and +65 min, respectively, after TSST-G onset). Cortisol will be determined with the Cortisol free in Saliva ELISA assay from Demeditec.

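### Hypothesis 1 claims a minimum cortisol rise of 1.5, but the only analysis named for it tests for any change over time, so a significant result would not show that the criterion was met

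*Protocol article*

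**What the plan says.** The Hypothesis 1 section has two parts. The first is general: "Participants in both groups (social support vs no social support) show an increase in stress responses comparable to that in previous studies". The second gives cortisol a size: "We expect a rise in the physiological parameter cortisol by at least 1.5 nmol/mL (Miller criterion".

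The Statistical Analysis section names one method for this question, an "analysis of variance with repeated measures to determine if the TSST procedure results in significant increases". The target is "significant increases in psychological and biological variables for all participants". The figure 1.5 does not appear in that section. The section does define an individual baseline-to-peak increase, but gives it another use: "This value will be obtained by subtracting the baseline value from the peak value. Multiple regressions will be calculated again with these adjusted values".

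The Salivary Cortisol section states: "The concentration of cortisol in saliva will be recorded in ng/mL". The criterion is printed in nmol/mL.

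**The concern.** The hypothesis sets a minimum size. The named test asks whether the time-point means differ at all. With a sample chosen for other comparisons, such a test can reject for rises well below 1.5, and a significant time effect could then be read as support for a size claim that was never examined.

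This matters for the main objective. The moderation hypotheses concern buffering or amplifying a stress response. If the average rise were small, a null moderation result would be hard to interpret, and a significant ANOVA would not reveal that. The Discussion acknowledges that there is no unstressed control group and that the effect of mask wearing on the procedure is hard to assess, so the size of the rise is worth knowing.

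The mismatch is separate from whether the arms are pooled or the test is directional. A one-sided, arm-specific test against zero would leave the same gap.

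**Working it through.** **Inputs from the article.** Criterion: 1.5. Seven cortisol samples, T0 to T6. Allocation 1:1. Sample size: "It is intended to recruit 154 participants (77 women"), including 20% for dropout; the Abstract gives 308.

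**Analysed number.** 154 / 1.2 = 128.3, so about 128, or 64 per arm. The effect size, alpha and power behind 154 are not stated. Assuming a two-group comparison with d = 0.5, two-sided alpha 0.05 and 80% power gives 64 per group, and 128 × 1.2 = 153.6, rounded up to 154. The target therefore fits an ordinary two-group comparison. Nothing ties it to the 1.5 criterion.

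**Assumptions.** The SD of an individual's change from baseline is not given, so I take 2 to 8 in the criterion's units. Alpha is 0.05 two-sided. The true mean rise is 0.75, half the criterion.

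**Test against zero.** For a paired change, SE = SD / √N and the noncentrality is 0.75 / SE. At N = 128 and SD 3, SE = 3 / 11.31 = 0.265 and the noncentrality is 2.83. Against a critical t of 1.98 the power is 0.80. The smallest significant observed mean is 1.98 × 0.265 = 0.52.

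| SD of change | Smallest significant mean, N=128 | P(significant), N=128 | N=154 | N=308 |
|---|---|---|---|---|
| 2 | 0.35 | 0.99 | 0.996 | >0.99 |
| 3 | 0.52 | 0.80 | 0.87 | 0.99 |
| 4 | 0.70 | 0.56 | 0.64 | 0.91 |
| 5 | 0.87 | 0.39 | 0.46 | 0.75 |
| 8 | 1.40 | 0.18 | 0.21 | 0.38 |

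At N = 128 the probability is at least 0.80 for an SD up to about 3.0 and at least 0.50 up to about 4.3.

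**Check with the omnibus test.** A simulated seven-sample repeated-measures ANOVA with Greenhouse-Geisser correction (N = 128, assumed response shape and correlation, peak mean rise 0.75) was significant in 98%, 77%, 44% and 25% of runs at SDs of about 2, 3, 4 and 5.

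**Group-mean reading of 1.5.** With the same true rise of 0.75 and N = 128, a one-sided 5% test of a mean rise of 1.5 or less would wrongly support the claim with probability below 0.001 for SDs up to 5, and 0.003 at SD 8.

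**Per-person reading of 1.5.** If changes are roughly normal with mean 0.75, the share above 1.5 is P(Z > 0.75 / SD): 35% at SD 2, 40% at SD 3, 44% at SD 5. A significant ANOVA can therefore coexist with most participants below the criterion.

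**Unit.** Assuming a molar mass of about 362 g/mol, 1.5 nmol/mL is 1.5 × 362 = 543 ng/mL. If a per-litre unit were meant, it would be about 0.54 ng/mL. The printed criterion cannot be set against the recorded values until this is settled.

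**The case against.** **The article is condensed.** One paragraph covers the analysis of five hypotheses, the full study protocol is an appendix not shown here, and an analysis plan may exist. How a cited criterion is tabulated is often left to such documents. This has weight, and the absence of a table or responder count alone would be no finding. But the article does name a test and its purpose for stress induction, and that test cannot decide the stated size. That part stands.

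**The criterion may be per person.** The hypothesis does not say, and the individual peak-minus-baseline value is what a per-person threshold would need. That is a fair reading. It does not close the gap, because the value is assigned to the regressions and is not compared with 1.5. It does rule out a remedy that presumes a group mean.

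**The size depends on an unknown SD.** This is correct. A reader might infer that a rise of half the criterion would be declared a confirmed response as a matter of course. The article does not support that: at an SD of 5 the probability is 0.39 for a single contrast and about 25% for the omnibus test, and nowhere does it say that the hypothesis will be accepted on the p-value alone.

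**The criterion may not carry much weight.** A reader might also infer that meeting 1.5 is the study's main evidence that the stressor worked. The Discussion instead justifies the missing unstressed control by the procedure being established, and the hypothesis covers psychological as well as biological responses. The stronger inference should not be drawn.

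**Conclusion.** The point holds in a limited form. The hypothesis states a minimum size and the named test has a null of no change, so significance does not establish the size. This is true at any SD, at 154 or 308 participants, and whether 1.5 is a mean or a per-person criterion.

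How often the gap would mislead cannot be fixed from the article. For a true mean rise of 0.75, significance is likely if the SD of change is about 3 or less at N = 128, and less likely than not above about 4.3. These figures rest on an assumed SD, alpha and response shape.

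The moderation regressions do not depend on this test. What is at risk is the wording of the conclusion on stress induction and the reading of any null moderation result.

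**What to change.** 1. Reconcile the unit of the criterion with the unit in which cortisol is recorded.
2. State whether 1.5 applies to the group mean or to each participant.
3. Keep the repeated-measures ANOVA as the description of the time course.
4. For cortisol, report in each arm the mean change from T0 to one prespecified post-stress sample, with a 95% confidence interval set beside 1.5, and the share of participants at or above 1.5. The baseline-to-peak value can be shown as well to cover delayed responses, but as a within-person maximum it is biased upward against a fixed threshold.
5. Claim a rise of at least 1.5 only if these results support it. For the group mean, an interval wholly above 1.5 supports the claim, one wholly below contradicts it, and one that spans 1.5 leaves it open. If the authors mean only that cortisol increases, reword the hypothesis that way.

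**Cost.** No new samples are needed, only one estimate, one interval and one count per arm. The size claim becomes harder to support than a test against zero. With 64 per arm and an assumed SD of 3, SE = 3 / 8 = 0.375, and the lower limit exceeds 1.5 only if the observed mean is above 1.5 + 2.00 × 0.375 = 2.25. I would not make that lower limit a pass/fail rule in each arm: a true mean of exactly 1.5 satisfies the hypothesis as worded, yet would fail such a rule about 97.5% of the time per arm.

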#### Hypothesis 2: Social Support × Social Motive Hypothesis

The affiliation motive moderates the effects of social support on stress responses. A higher affiliation motive of participants is associated with greater benefit from social support, that is, they will express lower psychobiological stress responses (better self-reported well-being, less perceived stress, lower heart rate, higher heart rate variability, and lower levels of cortisol and α-amylase). While the affiliation motive is expected to function as a stress buffer, the power motive is assumed to function as a stress amplifier. A higher power motive of participants is associated with greater negative impact from social support, that is, they will report lower well-being, more perceived stress, higher heart rate, lower heart rate variability, and higher levels of cortisol and α-amylase.

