#### Hypothesis 3: Motive-Specific Arousal Hypothesis 

Participants with strong affiliation and power motives respond to social support with arousal of self-reported motive-specific affect (ie, affiliation: joy and feeling socially related; power: feeling weak and inferior) and with an increase in motive-specific reproductive hormone responses* *(affiliation: progesterone; power: estradiol and testosterone).

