## Discussion

The aim of this study is to investigate whether social motives and participants’ sex moderate the effect of social support in stressful situations. We expect that participants with a strong affiliation motive will benefit from social support in terms of reduced psychobiological stress responses when being critically evaluated by others. For those participants, social support is supposed to serve as a stress buffer. In contrast, social support is expected to act as a stress amplifier in participants with a high-power motive, resulting in higher psychobiological stress responses.

To elucidate the influence of implicit social motives on affect in specific situations, we will record participants’ motive-specific affect. We postulate that participants with a high affiliation motive, will respond to social support with affiliation and an increase in progesterone. Participants with a high power motive will show feelings of inferiority and a decrease in testosterone or estradiol.

To explore the influence of implicit motives without bias, we also consider sex as a variable in our study. It is hypothesized that males exhibit a higher power motive and females exhibit a higher affiliation motive. This is expected to be reflected in motive-specific hormones.

Some studies have shown that social support has positive effects [72], while others have reported no, small, or adverse effects of social support [73,74]. With the introduction of implicit motives as moderator variables, as well as taking sex into account, we strive to explain why people react differently in same situations. Through this person-situation approach, we enable a more differentiated view on the effect of social support in stress situations. In summary, with this sophisticated view, we aim to provide a foundation that interventions could be designed in an individualized way and therefore only produce positive effects and no adverse effects.

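### The hormone regressions are run on two scores with no stated rule for which decides, and the second score, built for rises, is also applied to testosterone and estradiol, for which the Discussion predicts a fall.

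*Protocol article*

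**What the plan says.** The Statistical Analysis section of the protocol article deals with repeated hormone samples by a summary score: "the area under the curve with respect to increase will be calculated and used as a dependent variable". It then adds a second score, with this reason: "As an additional effort to ensure that participants with a delayed significant increase in their hormones will not be excluded". The definition is "This value will be obtained by subtracting the baseline value from the peak value", whatever the time of the peak. The consequence is "Multiple regressions will be calculated again with these adjusted values". The section does not rank the two results, limit the second score to particular hormones, or say whether the baseline sample T0 may itself be the peak.

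The expected direction for the power-motive hormones differs between sections:

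- Hypothesis 3 expects strongly motivated participants to respond to support "with an increase in motive-specific reproductive hormone responses", naming estradiol and testosterone for power and progesterone for affiliation.
- The Discussion says: "Participants with a high power motive will show feelings of inferiority and a decrease in testosterone or estradiol".
- The background on implicit motives reports falls in testosterone (men) and estradiol (women) when a strong power motive is frustrated.
- Hypothesis 4 expects relative increases: estradiol and progesterone in women, testosterone in men.

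Hypothesis 1, the stress-induction check, is analysed in another way: "We will perform an analysis of variance with repeated measures to determine if the TSST procedure results in significant increases".

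**The concern.** Two issues follow from the repeated regressions.

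First, two results will exist for each hormone test (cortisol in Hypothesis 2, the hormones in Hypothesis 3 and the hormone part of Hypothesis 4). With no rule for disagreement, the choice can be made after both are seen.

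Second, a maximum treats rises and falls differently. If a hormone dips at one sample and recovers, the maximum is taken from another sample and most of the dip is lost. The article predicts a fall in testosterone or estradiol in one place, so the repeat analysis could read as no effect for a reason unrelated to biology. Because the predicted sign is itself unsettled, a score that favours one sign is a poor referee.

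**Working it through.** **Inputs from the article.** Reproductive hormones are sampled at T0 (−11 min), T1 (0), T3 (+20) and T6 (+65). Allocation is 1:1. Methods gives 154 participants including 20% for dropout, and 154 / 1.2 ≈ 128, so 64 per arm. (The Abstract gives 308. A larger sample would raise all powers but would not remove the asymmetry.)

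**Assumptions, because the article gives no figures.** Normal values with SD 1, equal correlation of 0.6 to 0.8 between occasions, two-sided 5% tests. Unless stated, the peak is the highest of T1, T3 and T6.

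**The two scores.** With Y0, Y1, Y3 and Y6 for the samples, the trapezoid areas are 5.5·Y0 + 15.5·Y1 + 32.5·Y3 + 22.5·Y6. Subtracting 76 min × Y0 gives

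AUCi = −70.5·Y0 + 15.5·Y1 + 32.5·Y3 + 22.5·Y6.

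This is linear, so a rise and a fall of equal size count equally. The second score, D = max(Y1, Y3, Y6) − Y0, is not linear. Take a noise-free person at 0 throughout except T3. A rise of 1 SD gives AUCi = +32.5 and D = +1. A fall of 1 SD gives AUCi = −32.5 and D = 0.

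**No true change.** The expected maximum of three independent standard normals is about 0.846, so E(D) = 0.846 × √(1 − ρ): 0.846 × 0.632 = 0.54 SD at ρ = 0.6, and 0.846 × 0.447 = 0.38 SD at ρ = 0.8. T0 is the highest of four exchangeable samples one time in four, so about 75% of people score above zero. AUCi averages zero. The offset is the same in both arms, and the simulated rejection rate of the support-by-motive test on D stayed near 5%.

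**Either score counted as support.** The two scores correlate at about 0.9. Simulated false-positive rate per interaction test: about 7 to 8%, against 1 − 0.95² = 9.75% if they were independent.

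**Power, simulated (ranges run over ρ = 0.6 to 0.8; runs differ by a point or two).** The interaction has slope 0.35 SD per motive SD in the supported arm.

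| Samples that change | 0.7 SD fall between arms: AUCi | Same: peak minus baseline | Support × motive: AUCi | Same: peak minus baseline |
|---|---|---|---|---|
| T3 only | 71–93% | 15–20% | 23–41% | 12–25% |
| Two post-baseline samples (interaction: T3 and T6) | 95–100% | 68–86% | 54–83% | 37–60% |
| All post-baseline samples | 100% | about 100% | 73–96% | 69–93% |

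A 0.7 SD rise at T3 only gives peak minus baseline 68 to 98% power, so the loss is specific to falls. The gap is narrower for the interaction because the effect is proportional to a centred motive score: some supported participants move up and some down, and the score still sees the rises. If T0 may be the peak, power for a fall at T3 and T6 drops further, to 58 to 71%. With uncorrelated occasions the T3-only comparison is 35% (AUCi) against 12%, in the same order.

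**The case against.** AUCi is named first as the dependent variable, and the second score is introduced as an additional effort with a stated purpose. A reader may fairly take this as a main analysis plus a supplement, and an analysis plan that is not shown may say so outright. That stands as mitigation. But the article itself fixes the second score and applies it to hormones without distinction, and that can be judged from the article alone.

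The score also does what it was designed for. For a 0.7 SD rise at T6 only, its power is 69 to 97% against 40 to 67% for AUCi. It is therefore useful where a rise is expected, including progesterone, for which Hypothesis 3 and the Discussion agree on an increase. Removing it for every hormone would go too far.

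Four stronger readings are tempting, and the article does not support them:

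- *Every hormone hypothesis is tested twice.* Hypothesis 1 goes to a repeated-measures analysis of variance. Only the regressions are repeated.
- *The score is nearly blind to any decrease.* That holds for a brief fall that spares other post-baseline samples. Nothing in the article confines the fall to T3, and support is given before T1, so a fall across all later samples is possible and would be detected.
- *The positive average under no change biases the tests.* It is equal in both arms and leaves the interaction test near 5%.
- *The repeat scoring creates a large multiplicity problem.* The longer list in Hypothesis 2 ("better self-reported well-being, less perceived stress, lower heart rate, higher heart rate variability, and lower levels of cortisol and α-amylase", for two motives) is a separate matter of outcome hierarchy, which an article commonly leaves to the analysis plan.

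**Conclusion.** The point holds in limited form. The regression-based hormone tests have two scores and no stated decision rule, at a cost of about 2 to 3 percentage points in false-positive rate per test if either may count. The second score is poorly matched to testosterone and estradiol if they fall as the Discussion predicts. The loss ranges from severe (a fall at one sample) through moderate (two samples) to none (all post-baseline samples), and it is smaller for the planned support-by-motive interaction than for a plain comparison of arms. The average of about +0.4 to +0.5 SD when nothing happens must not be read as evidence of a rise.

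The sizes rest on assumed normal values, equal correlations and 128 analysed participants. A diurnal trend or another correlation pattern would change the figures, but the asymmetry comes from taking a maximum. The conflict in direction between Hypothesis 3 and the Discussion needs no assumption.

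**What to change.** - State that AUCi is the deciding score for all hormone regressions, and that a disagreement with the second score does not change the conclusion.
- Label peak minus baseline a sensitivity analysis for outcomes where an increase is expected (cortisol, progesterone), and say whether T0 can be the peak.
- For testosterone and estradiol, where a decrease is predicted, leave the score out or replace it with one that treats rises and falls alike.
- Reconcile the predicted direction for these two hormones between Hypothesis 3 and the Discussion, checking it against the relative increases in Hypothesis 4, before the hormone results are seen.
- Do not report a positive mean of the peak score as a hormone rise.

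The cost is wording only, with no new data collection. The downside is that fewer results can be called confirmatory.
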